## Methods

### Objectives

The primary objective of the CERT-D is to evaluate whether treating cognition, emotion processing, and social cognition leads to immediate and longitudinal benefit in psychosocial functioning. To achieve this objective, participants will complete either a personalized or standard (non-personalized) treatment devoted to increasing performance in these domains. Participants in the personalized group will receive a tailored treatment incorporating a greater number of sessions devoted to their domain(s) of primary baseline dysfunction. By contrast, the standard treatment group will complete a pre-established battery of treatment independent of baseline deficits.

The key hypotheses and aims of the current study are as follows:
*Hypothesis 1*:Overall, psychosocial functioning will be improved at 8 weeks [end of randomized, controlled treatment (RCT)] relative to baseline. Psychosocial functioning in the observational period (post-RCT) will not decline at 3 and 6 months relative to post-RCT baseline.*Related Aim*:To evaluate which subdomains of psychosocial function (e.g., autonomy, social relationships) are sensitive to change over time from the CERT-D.*Hypothesis 2*:Performance in secondary outcome measures will improve at 8 weeks relative to baseline, and will be retained over a 6-month observational period. Secondary outcomes include occupational functioning, cognitive failures, functional disability, resilience, and depression symptom severity.*Hypothesis 3*:It is expected that the personalized treatment group will display greater psychosocial improvement at 8 weeks (compared to baseline) than subjects who complete a standard treatment.*Hypothesis 4*:Biological and genomic signatures will be associated with psychosocial functioning, as well as cognitive, emotional, and social cognitive performance.

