### Personalization

Given the multifaceted nature of impairment in depression, it is reasonable to assume that deficits will not occur in a uniform nature within individuals. Certain individuals may be disadvantaged specifically in domains of emotional processing, while others are more disadvantaged in terms of cold cognitive ability or social cognition. Previous interventions may not have led to consistent improvements in psychosocial functioning because individual differences in domain-specific impairment were not addressed. In fact, existing interventions assume that group means (i.e., norms) reflect impairment at an individual level, and hence that a generalized treatment approach is sufficient. Given the heterogeneity of impairment observed between individuals with MDD (12), it is possible that a standard treatment approach is not optimal (50). In particular, standard treatment approaches may misappropriate resources and time to clinical domains which are not relevant or helpful to the individual. In contrast, personalized approaches tailor treatment by targeting baseline deficits within individuals, enabling treatment to focus on impaired domains, while also spending less time addressing more functional domains. Personalization may improve treatment efficiency and efficacy, in contrast to the traditional standard approach.

The current investigation will evaluate the personalized approach, by comparing psychosocial functioning following a personalized intervention and a standard (i.e., non-personalized) intervention. The personalized intervention will tailor treatment tasks around baseline individual deficits, such that the individual’s most impaired domains receive the greatest attention. Given the importance of cognition, emotion processing, and social cognition in determining psychosocial functioning, the CERT-D treatment will be tailored by patterns of impairment observed in these three domains. For example, a participant who demonstrates severe cognitive impairment will receive a greater number of treatment sessions devoted to cognition, with fewer sessions devoted to emotion processing and social cognition. Overall, it expected that both personalized and standard treatments will result in improved psychosocial functioning, which is expected to be retained over a 6-month observational period. However, it is predicted that the clinical effect on psychosocial function will be greater following personalized, relative to standard, treatment.

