### Study Design and Recruitment

The CERT-D study will commence in July 2017. The study will be a RCT, comparing the clinical efficacy of a personalized and standard intervention. Psychosocial functioning is considered the primary outcome. An effect size of approximately *d* = 0.5 is expected with regards to change in psychosocial function over the intervention. Given the intended sample size of 100, the study will achieve statistical power of 89% (1 − β = 89). The rationale for this “medium” effect size is that previous interventions have found positive outcomes approximate to this magnitude (5, 35), for example in cognitive functioning.

The trial will include 16 treatment sessions designed to improve cognition, emotion processing, and social cognition administered over an 8-week period. Assessments will occur at baseline, 4 weeks (mid-RCT), 8 weeks (end of RCT), and in the observational period at baseline (week 9) and 3 and 6 months post-RCT (see Figure 1). Assessments will measure psychosocial functioning, cognition, emotional state, social cognition, as well as occupational functioning, depression symptom severity, functional disability, cognitive failures, and resilience. Three assessment visits will also include taking blood for biomarker and genetic analysis. Recruitment will include individuals between the ages of 18 and 75, who will be invited to participate *via* research clinics of the Department of Psychiatry, University of Adelaide, and within the Central Health Network in Adelaide, South Australia. It could be argued that the age range should be restricted to younger adults (<60), such that subjects with geriatric depression are excluded. However, recent work has suggested that cognitive training strategies are efficacious in the treatment of geriatric depression (47, 51, 52). Given the current intervention shares many components of traditional cognitive training, it is suggested that the CERT-D intervention should benefit older (i.e., 60–75 years) patients.

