## Intervention Outcomes, Analyses, and Dissemination

The primary outcome of the CERT-D will be psychosocial functioning. Specifically, it is expected that psychosocial functioning will improve at 8 weeks (end of RCT) relative to baseline. Post-RCT psychosocial functioning is expected to be maintained over the 6 months observational period. Performance in secondary outcome measures is expected to demonstrate a similar effect of treatment. Secondary outcomes include depression symptom severity, occupational functioning, resilience, functional disability, and perceived cognitive failures. In addition, the personalized treatment group is expected to show greater improvement over time relative to the standard treatment group. Finally, the association between biomarkers and psychosocial and cognitive performance before and following treatment will be evaluated.

Statistical analyses will be performed with a mixed model ANOVA with time (baseline, 8 weeks, baseline post-RCT, 3 months post-RCT, 6 months post-RCT) and treatment type (personalized, standard) as independent variables. Psychosocial functioning (FAST score) will be the dependent variable. It is expected that overall psychosocial functioning will improve at post-treatment relative to baseline, and that this improvement will be greater in the personalized treatment arm relative to the standard treatment arm. Biomarker analyses require specifically tailored software and will ultimately be entered into simple and stepwise linear regression analyses. These analyses will determine whether individual biomarkers (e.g., CRP), or combinations of biomarkers, are related to cognition (i.e., THINC-it performance) or psychosocial functioning.

Within the personalized treatment group, further analyses will evaluate whether there are any differences in psychosocial functioning owing to the domain-specific treatment groups. That is, will there be any differences in post-RCT psychosocial functioning between the high cognition, high emotion, and high social cognition treatment groups? Given the novelty of the current treatments, these analyses will be exploratory. As with the primary outcome, analyses for this outcome will be conducted with mixed model ANOVAs.

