A possible disadvantage of administering training across three domains is that treatment benefits to cold cognitive functioning (e.g., executive functioning) will be attenuated in comparison to traditional cognitive remediation. Reduced executive gains in the CERT-D treatment could result from the equal emphasis given to social, emotional, and cognitive domains, as opposed to focusing purely on cold cognition. However, we do not anticipate this issue to be a crucial issue for two key reasons: (1) emotional and social–cognitive training demand similar cognitive effort and are equally complex in comparison to traditional cognitive training. As a result, emotional and social training may also benefit executive functioning. (2) Individuals who demonstrate significantly impaired cold cognition will be allocated to the “High Cognition” program within the personalized arm. This treatment program emphasizes cognitive treatment above emotional and social domains, and will hence evaluate the efficacy of predominantly cognitive training, relative to training all three domains in the “standard” treatment group. If cognition training alone is identified as having greater clinical efficacy than the integrated training approach, then this finding will also contribute to the value of the current study.

In summary, the CERT-D will make three primary contributions: (1) the evaluation of a novel psychological treatment for depression. Psychosocial function is considered the primary outcome, and is expected to be improved by integrated treatment of underlying domains. (2) The comparison of the relative clinical efficacy of personalized and standard treatment approaches. Taking baseline deficits into account may enable more efficient and effective psychosocial recovery, as impaired domains receive greater attention. In combination, contributions (1) and (2) may lead to the development of an intervention which could be conducted in parallel or in lieu of other treatments for depression. (3) The current study will also improve our understanding of the genomic, neurological and biological correlates of psychosocial and cognitive dysfunction in depression. Taken together, these findings will advance the field of personalized psychiatry by evaluating the relative efficacy of a standard and personalized treatment approach, in addition to testing the overall value of targeting psychosocial deficits in MDD.

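### The causal primary objective is tested as uncontrolled change from baseline pooled over two treated arms, so the time effect cannot be attributed to CERT-D

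*Protocol article*

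**What the plan says.** The Objectives section puts the primary objective in causal terms: "The primary objective of the CERT-D is to evaluate whether treating cognition, emotion processing, and social cognition leads to immediate and longitudinal benefit". The first test of it is Hypothesis 1: "Overall, psychosocial functioning will be improved at 8 weeks [end of randomized, controlled treatment (RCT)] relative to baseline". Hypothesis 1 adds that functioning will not decline over the observational period, and Hypothesis 2 repeats the before-after pattern for the secondary outcomes. The Related Aim under Hypothesis 1 attributes the change to treatment, asking which subdomains are "sensitive to change over time from the CERT-D".

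Study Design and Recruitment describes the trial as "comparing the clinical efficacy of a personalized and standard intervention". The sections on personalized and standard treatment show that participants in either arm complete CERT-D sessions, and the Personalization section expects both arms to gain: "it expected that both personalized and standard treatments will result in improved psychosocial functioning". No third group is described.

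The section on outcomes and analyses gives the pooled result first ("It is expected that overall psychosocial functioning will improve at post-treatment relative to baseline") and then the difference between arms. The model is a mixed ANOVA with five time levels and treatment type. The Discussion lists evaluation of the novel treatment as a contribution separate from the comparison of arms.

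**The concern.** Randomization protects one contrast, personalized against standard. That contrast says whether personalization adds something, not whether CERT-D works. The objective, "whether treating cognition, emotion processing, and social cognition leads to immediate and longitudinal benefit in psychosocial functioning", is addressed by the time effect, and every participant is treated. Anything else that moves FAST scores between baseline and week 8 enters that effect in full.

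If Hypothesis 3 came out null and the time effect came out significant, the trial could still be said to have met its stated primary objective. What is at stake is the trial's lead conclusion. An analysis plan could not repair this, because it cannot supply a comparator that the design lacks.

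**Working it through.** **1. Which contrast has a control**

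| Hypothesis | Contrast | Control for change over time |
|---|---|---|
| 1 (FAST) | 8 weeks against baseline, arms pooled | none |
| 2 (secondary outcomes) | 8 weeks against baseline, arms pooled | none |
| 3 (FAST) | change, personalized against standard | the other randomized arm |

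The FAST rater is blind to arm (Psychosocial Functioning section). This protects Hypothesis 3. It does not protect a before-after contrast pooled over arms.

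**2. The plan's own figure**

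Study Design and Recruitment gives d = 0.5 for change over the intervention, N = 100 and power of 89%. It does not give alpha, sidedness, allocation ratio or the correlation between visits. With two-sided 5%, no dropout and, where arms are compared, 50 per arm:

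- Paired test, n = 100: noncentrality 0.5 × √100 = 5, power 99.9%.
- Two-sample test, 50 per arm: 0.5 × √(50/2) = 2.5, power 70.5% (normal) or 69.7% (t).
- Between-arm main effect in a repeated-measures ANOVA with five time levels, f = 0.25 and an assumed correlation of 0.5: λ = 0.25² × 100 × 5 / (1 + 4 × 0.5) = 10.42, power 89.2%.
- Between-arm change score, d on the raw SD, assumed correlation 0.7: standardized difference 0.5/√(2 × 0.3) = 0.645, power 89.2%.

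So 89% can be reached under more than one unstated assumption. It is not shown to be wrong, but the reader cannot tell which hypothesis it serves.

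**3. Chance of a significant pooled improvement if CERT-D does nothing**

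Assumptions: paired t-test, n = 100, df = 99, two-sided 5%, no dropout. Let g be the background change in SDs of the change score; noncentrality is g × √100 = 10g. The range of g is assumed, since the protocol gives no value.

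| g | 10g | P(significant improvement) |
|---|---|---|
| 0 | 0 | 2.5% |
| 0.1 | 1 | 17% |
| 0.2 | 2 | 51% |
| 0.3 | 3 | 84% |
| 0.4 | 4 | 98% |

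The paired test stands in for the 8-week against baseline contrast within the planned mixed ANOVA. It is not the five-level overall time test.

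**4. Power if the efficacy claim rests on Hypothesis 3**

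Assumptions: 50 per arm, two-sided 5%, no dropout.

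- Between-arm d = 0.5, unadjusted: about 70% (step 2).
- Baseline-adjusted, d on the raw SD, effective d = 0.5/√(1 − ρ²): ρ = 0.5 gives 0.577 and 82%; ρ = 0.6 gives 0.625 and 87%; ρ = 0.7 gives 0.700 and 93%.
- Between-arm d = 0.25, unadjusted: 0.25 × √(50/2) = 1.25, power about 24%.

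**The case against.** The best counter-argument is in the protocol's Introduction, which reports that psychosocial dysfunction seems to persist even in patients whose symptoms have resolved. On that premise, remission of depression need not carry FAST with it, and spontaneous improvement over 8 weeks is less certain. This stands, and it is why the lower rows of the table in step 3 matter. It does not replace a concurrent control. Expectancy remains, as does parallel care: the Ethics section refers to a participant's treating psychiatrist or GP. The argument is also weaker for Hypothesis 2, which includes depression severity and self-report scales.

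Two further mechanisms deserve little weight. Regression to the mean is possible but of unknown size, because entry is by diagnosis and mild to moderate severity, not by a FAST threshold, and severe cases are excluded. Retest effects should be weak for a clinician-administered scale.

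A reader might infer two stronger points that the text does not support. The first is that a significant time effect is almost certain whatever CERT-D does. Under the assumed range the probability runs from 17% to 98%, and nothing in the protocol fixes where it lies. The second is that the Discussion moves from the time effect to replacing other treatments. The sentence is hedged ("may lead to the development of an intervention which could be conducted in parallel or in lieu of other treatments for depression"), and it draws on the evaluation of the treatment and the comparison of arms together. Its weakness is only that the first of these rests on the uncontrolled contrast.

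It is also fair to say that Hypotheses 1 and 2 are already worded as change from baseline, and that the randomized comparison is already a key hypothesis.

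**Conclusion.** The point holds in a limited form. The primary objective and the Related Aim make a causal claim, the contrast offered for it has no control, and the Discussion does not acknowledge this. Hypothesis 3 is sound and unaffected.

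The size depends on a background change that the protocol does not give. Even 0.2 SD of the change score would yield a significant pooled improvement about half the time with no CERT-D effect, against a nominal 2.5% in that direction. The finding does not say that such change will occur, that CERT-D is ineffective, or that the 89% power is wrong. It says that the time effect, whatever its size, cannot establish that CERT-D caused it.

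**What to change.** - Reword the primary objective and the Related Aim so that they describe change during CERT-D, not change caused by it.
- Report Hypotheses 1 and 2 as within-group change with confidence intervals, and state explicitly that it cannot be attributed to CERT-D.
- Bring the efficacy claims in the Abstract, in the summary that closes the Introduction and in the Discussion into line. Keep efficacy language for the randomized comparison in Hypothesis 3.
- State which hypothesis the 89% power refers to, with its alpha, sidedness, allocation and assumed correlation.

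**Cost.** The edits are to wording, but they touch the stated objective of a registered, ethics-approved trial. The claim becomes more modest, and whether CERT-D itself works stays unanswered. Whether Hypothesis 3 should also become the single confirmatory test is more debatable. If it does, power ranges from about 24% to about 93% over the assumptions in step 4 and should be stated openly. Reaching 89% unadjusted at a between-arm d of 0.5 would need 2 × (1.960 + 1.227)² / 0.5² = 81.3, rounded up to 82 per arm or 164 in total.

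If the sponsor wants to answer the causal question, a concurrent control and a larger trial are needed. A third arm within the present 100 (33 per arm) gives about 52% power per pairwise comparison at d = 0.5.

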### Study Design and Recruitment

The CERT-D study will commence in July 2017. The study will be a RCT, comparing the clinical efficacy of a personalized and standard intervention. Psychosocial functioning is considered the primary outcome. An effect size of approximately *d* = 0.5 is expected with regards to change in psychosocial function over the intervention. Given the intended sample size of 100, the study will achieve statistical power of 89% (1 − β = 89). The rationale for this “medium” effect size is that previous interventions have found positive outcomes approximate to this magnitude (5, 35), for example in cognitive functioning.

The trial will include 16 treatment sessions designed to improve cognition, emotion processing, and social cognition administered over an 8-week period. Assessments will occur at baseline, 4 weeks (mid-RCT), 8 weeks (end of RCT), and in the observational period at baseline (week 9) and 3 and 6 months post-RCT (see Figure 1). Assessments will measure psychosocial functioning, cognition, emotional state, social cognition, as well as occupational functioning, depression symptom severity, functional disability, cognitive failures, and resilience. Three assessment visits will also include taking blood for biomarker and genetic analysis. Recruitment will include individuals between the ages of 18 and 75, who will be invited to participate *via* research clinics of the Department of Psychiatry, University of Adelaide, and within the Central Health Network in Adelaide, South Australia. It could be argued that the age range should be restricted to younger adults (<60), such that subjects with geriatric depression are excluded. However, recent work has suggested that cognitive training strategies are efficacious in the treatment of geriatric depression (47, 51, 52). Given the current intervention shares many components of traditional cognitive training, it is suggested that the CERT-D intervention should benefit older (i.e., 60–75 years) patients.

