A large body of work has investigated the selective treatment of impaired cognition in depression with cognitive remediation programs (2, 5, 26), which typically involve repeated completion of cognitive tasks over several weeks. The results of such programs generally reveal that patients improve on measures of executive, visuospatial, and verbal function (2). These results support the theory that repeated activation of brain regions *via* cognitive treatment increases neuroplasticity and improves neural function (27). Although cognitive gains following remediation programs are relatively consistent, the transfer of this benefit to occupational function, resilience, and psychosocial functioning are not well established (15). It is possible that transfer of cognitive skills does not reliably occur because remediation programs do not also address impaired social cognitive skills and emotional processing, which may negatively interact with cognition on depression outcomes. The following paragraphs discuss the role of emotion processing and social cognition in MDD, and highlight how an integrated and personalized treatment approach may be critical to maximizing treatment outcomes.

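### The stated 89% power does not follow from N = 100 and d = 0.5 for either hypothesis on 8-week FAST change: conventional assumptions give about 70% between arms and about 99.9% pre-post

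*Protocol article*

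**What the plan says.** The power statement is in Methods, Study Design and Recruitment. That section describes the design as follows: "The study will be a RCT, comparing the clinical efficacy of a personalized and standard intervention". It puts the effect size at about d = 0.5, which "is expected with regards to change in psychosocial function over the intervention", and then gives the result: "Given the intended sample size of 100, the study will achieve statistical power of 89" per cent. It does not say which comparison the figure belongs to, at what alpha, one- or two-sided, or which SD scales d.

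Objectives contains two hypotheses on 8-week change in psychosocial function:

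- Hypothesis 1, arms pooled: "Overall, psychosocial functioning will be improved at 8 weeks" relative to baseline.
- Hypothesis 3, between arms: "the personalized treatment group will display greater psychosocial improvement at 8 weeks (compared to baseline) than subjects who complete a standard treatment".

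The section Intervention Outcomes, Analyses, and Dissemination plans a mixed model ANOVA of the FAST score, with five time points and two treatment types.

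**The concern.** The article prints sample size, effect size and power side by side, so a reader will take the third to follow from the first two. The usual calculation for a two-arm trial of 100 participants at d = 0.5 gives a figure well below 89%. The usual calculation for a pre-post change in 100 participants gives one well above it.

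The randomized comparison of personalized with standard treatment is where this matters most. If the 89% is read as its power, the type II error appears to be 11%. Under conventional assumptions it is about 30%. A reader who relied on 89% would give a non-significant difference between arms more weight as evidence against personalization than the design supports.

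**Working it through.** **Inputs from the article.** N = 100; d = 0.5 on change in psychosocial function; two randomized arms; stated power 89%.

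**Assumptions, because the article gives no value.** 1:1 allocation (50 per arm), two-sided alpha 0.05, d scaled by the SD of change, complete data. Variations are shown in steps 3 and 4.

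**Step 1. Hypothesis 3, difference between arms in change.** Two-sample t test with noncentrality d × √(n/2), where n is the number per arm.

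- 0.5 × √(50/2) = 2.5 on 98 degrees of freedom; two-sided critical value 1.984.
- Power = 69.7%. The normal approximation gives Φ(2.5 − 1.96) = 70.5%.
- One-sided at 0.05: 79.9%.
- The 8-week contrast within the five-visit ANOVA, using pooled error: 70.3%.

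With 50 per arm the detectable difference is d = 0.57 at 80% power and d = 0.64 at 89%.

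**Step 2. Hypothesis 1, pooled change from baseline to 8 weeks.** Paired t test with noncentrality d × √N.

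- 0.5 × √100 = 5.0 on 99 degrees of freedom.
- Power = 99.86%.
- If d is in raw-score SD units and r is the baseline-to-8-week correlation, the standardized change is 0.5/√(2(1 − r)). At r = 0 this is 0.354, and power is 93.8%. It rises with r, so 89% is not reached at any non-negative correlation.

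The stated 89% is therefore too high for Hypothesis 3 and too low for Hypothesis 1.

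**Step 3. What would give 89% for Hypothesis 3?**

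*Change scores with d in raw-score SD units.* The effective d is 0.5/√(2(1 − r)).

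| r | effective d | power |
|---|---|---|
| 0 | 0.354 | 42% |
| 0.3 | 0.423 | 55% |
| 0.5 | 0.500 | 70% |
| 0.6 | 0.559 | 79% |
| 0.7 | 0.645 | 89% |
| 0.8 | 0.791 | 97% |

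*Baseline-adjusted analysis with d in raw-score SD units.* The effective d is 0.5/√(1 − r²). At r = 0.63 this is 0.5/√(1 − 0.397) = 0.644, and power is 89.0%.

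*One-sided alpha of 0.10 with d in SD-of-change units.* Power is 88.6%.

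Each route needs a correlation and scaling, or an alpha, that the article does not give.

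**Step 4. A possible origin (inference only).** The arm main effect in a repeated-measures ANOVA has noncentrality λ = f² × N × m/(1 + (m − 1)ρ). With f = 0.25 (that is, d/2), m = 5 visits and ρ = 0.5:

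- λ = 0.0625 × 100 × 5/(1 + 4 × 0.5) = 31.25/3 = 10.42.
- Power on F(1, 98) = 89.2%.

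This matches the stated figure, and five is the number of visits in the planned ANOVA. But the effect averages the arm difference over all visits, including baseline, where randomization makes the expected difference zero. Hypothesis 3 concerns greater improvement from baseline to 8 weeks, which is an arm-by-time contrast. A related contrast, the mean of the four post-baseline visits minus baseline with a sustained difference, gives 88.4%; it is not Hypothesis 3 either.

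**The case against.** The best defence is that d has no stated standardizer. Tying it to change says what it describes, not which SD divides it. With raw-score scaling and a correlation near 0.70, 89% is a legitimate power for Hypothesis 3. This stands. A reader might infer that 89% is the power of no hypothesis in the protocol, or that the trial simply delivers 70%. The article supports neither: the 70% rests on assumed alpha, sidedness, allocation and scaling. What remains is that 89% cannot be obtained from the printed inputs, and that on raw-score scaling the answer ranges from 42% to 97% with a correlation that is not given.

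It can also be said that the figure was never meant for Hypothesis 3. The outcomes section presents the primary expectation as improvement at 8 weeks over baseline, and the protocol does not designate the between-arm comparison as the primary test. This stands too, and it rules out treating Hypothesis 3 as the named primary test. It does not rescue the 89%, since the pre-post test has about 99.9%.

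Two further criticisms are tempting and are not made here. One is that no dropout is allowed for. A condensed article may leave that to the full protocol, and whether 100 means enrolled or evaluable is not stated. The other is that d = 0.5 is optimistic, because the introduction says of cognitive remediation that "the transfer of this benefit to occupational function, resilience, and psychosocial functioning are not well established". The introduction also reports, under Social Cognition, that cognitive training has improved psychosocial functioning. Cognition is offered only as an example when d is justified, and the cited studies are not at hand.

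**Conclusion.** The point holds as an inconsistency between a stated power and the inputs printed beside it. With two-sided 5%, 1:1 allocation, d in SD-of-change units and complete data, the inputs give about 70% for Hypothesis 3 and about 99.9% for the pooled 8-week change in Hypothesis 1. The gap for the between-arm comparison is about 19 percentage points (89 − 70), and one-sided testing at 5% still leaves it at 80%. The figure may come from a valid calculation for a different effect or under undeclared assumptions, so it should not be called an arithmetic slip. As printed, a reader cannot attach it to either hypothesis.

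**What to change.** Replace the 89% sentence with two statements, each giving its test, alpha, sidedness and the SD that scales d:

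- Hypothesis 1, pooled change from baseline to 8 weeks: about 99.9% at d = 0.5 with 100 pairs.
- Hypothesis 3, personalized versus standard on 8-week change: about 70% at d = 0.5 on change with 50 per arm, two-sided 5%; detectable difference d = 0.57 at 80% power.

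If the sponsor wishes to keep 89% for Hypothesis 3, the text should state the analysis, the scaling and the correlation that produce it. If the figure came from the arm main effect averaged over visits, it should not be presented as the power for Hypothesis 3.

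The cost is one paragraph of wording and a less favourable figure for the between-arm comparison. Enrolment, design, analysis and the choice of primary hypothesis stay as they are.
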